# BPSDiary study protocol: a multi-center randomized controlled trial to compare the efficacy of a BPSD diary vs. standard care in reducing caregiver's burden

**DOI:** 10.3389/frdem.2023.1301280

**Published:** 2023-12-18

**Keywords:** BPSD, dementia, protocol, diary, behavior

## Abstract

**Trial registry:**

NCT05977855.

## 1 Introduction

The behavioral and psychological symptoms of dementia (BPSD) are a heterogeneous set of psychological reactions, psychiatric symptoms, and behavioral abnormalities that are present in persons with dementia (PwD) due to any etiology (D'antonio et al., 2022). These have been grouped in different clusters across different studies. One of the most common classifications divides them into five clusters: psychosis (delusions and hallucinations), affective symptoms (anxiety and depression), apathy, psychomotor symptoms (irritability, aberrant motor behaviors, agitation), and mania (euphoria and disinhibition). In Italy, the most common BPSD seem to be agitation, apathy, depression, psychosis, and aggression (D'antonio et al., 2022). It is likely that cultural and ethnic differences might partially explain the heterogeneity and relevance of BPSD across different countries and settings, as well as caregivers' responses (Abe et al., 2015).

BPSD are extremely relevant for PwD, as they are associated with a faster cognitive decline, loss of independence, falls, and institutionalization (Calsolaro et al., 2021). BPSD might be present across all stages of dementia, and even predate it (in the so-called mild behavioral impairment, MBI) (Ismail et al., 2017). Specific BPSD, such as apathy, might also predict conversion from mild cognitive impairment to dementia (Fresnais et al., 2022).

Several instruments have been proposed to assess BPSD. More than sixty scales and tools have been developed, the most commonly used probably being the Neuropsychiatric Inventory (NPI); however, none of them seems to satisfactorily address all relevant aspects of BPSD (Pozzi et al., 2023). Most instruments are limited by the high degree of recall bias, lack of direct observation, and length (D'antonio et al., 2022). Finally, an intrinsic risk using broad tools such as the NPI is the imprecise evaluation of BPSD as a unitary construct, aggregating symptoms with different biological basis and treatments (Cho et al., 2021).

Several modifiable and non-modifiable risk factors for BPSD have been identified in the literature. Inconclusive results have been published for APOE4, while polymorphisms in other genes, such as COMT, serotonin receptor 2A and IL-1β seem to correlate with specific BPSD (Flirski et al., 2011). Other non-modifiable “background factors” might be low education and female gender (Chang et al., 2020). On the contrary, “proximal factors,” which are temporally close to BPSD, might be potentially modifiable, and mostly include triggers and relational aspects between PwD and their caregivers (Cho et al., 2021; Nagata et al., 2022).

Current guidelines suggest to address proximal factors with non-pharmacological strategies as a first line treatment (Calsolaro et al., 2021). In practice, psychotropic medication are still largely used, possibly with the exception of BPSD pertaining to eating and sleeping (D'antonio et al., 2022). However, antipsychotics have several side effects (D'antonio et al., 2022), and despite FDA and European Medicine Agency black-box warnings they are often used for long periods, with an increasing risk of parkinsonism, sedation, falls, stroke, cognitive decline and death (Calsolaro et al., 2021). Nevertheless, the use of antipsychotics, acetylcholinesterase inhibitors and memantine seems to be associated with a reduced caregiver burden (Levy et al., 2012).

Non-pharmacological algorithms include DICE (Describe, Investigate, Create, Evaluate) (Kales et al., 2019) and DATE (Describe & Measure, Analyze, Treat, Evaluate) (Cho et al., 2021). Both rely on precise characterization of triggers to find optimal solution to address BPSD. Functional analysis is generally based on ABC approach, evaluating antecedent (trigger), behavior description and consequence. A meta-analysis demonstrated that functional analysis with tailored strategies for PwD and caregivers positively impact burdensome BPSD frequency and caregivers' reaction, but has no effect on incidence or severity of BPSD, mood or caregiver burden (Moniz Cook et al., 2008). In Italy, caregiver education is the most common non-pharmacological intervention, used by 86% of caregivers as a fist line (D'antonio et al., 2022).

An unmet need for physicians is the availably of more objective tools for severity, frequency and context of BPSD, in order to apply non-pharmacological strategies (Loi and Lautenschlager, 2017). In Italy, 93% of physicians working in the field of dementia would be interested in a new tool to address BPSD, which reflects the unsatisfactory nature of current options (D'antonio et al., 2022).

Among BPSD, those belonging to the HIDA domain (hyperactivity, impulsivity, irritability, disinhibition, aggression, agitation) seem to be the most difficult to treat (Van der Linde et al., 2014; Keszycki et al., 2019). Person-centered strategies, including positive and significant social interactions, reminiscence therapy among others, seem to have a beneficial effect, albeit modest (Keszycki et al., 2019). A recent study evaluated caregiver burden and BPSD assessment with daily phone interviews over the course of eight days, showing that the quality of the relationship between caregivers and PwD attenuates caregivers stress related to BPSD (Chunga et al., 2021). Several instruments exist to evaluate caregiver burden, the most common being the Zarit Burden Interview (ZBI) (Melo et al., 2011; Liu et al., 2017; Griffiths et al., 2018; Evans et al., 2021; Jhang et al., 2021; Kanemoto et al., 2021), whose Italian version has been validated and is freely available (Chattat et al., 2011). The ZBI includes 22 questions, each scored with a 0–4 Likert scale, with a total score above 25 indicating a clinically significant burden. Generally speaking, the most burdensome BPSD include delusions, aggression, aberrant motor behavior, agitation and irritability, which substantially overlap with the HIDA domain (Fauth and Gibbons, 2014; Hiyoshi-Taniguchi et al., 2018).

A rather neglected field is satisfaction of caregivers for care provided by physicians to PwD. No instrument for healthcare satisfaction has been validated in caregivers of PwD, or in BPSD, and many instruments seem excessively long.^1^ On the other hand, there is a lack of instruments evaluating physicians satisfaction in treating PwD.

The main idea of our study is to make caregiver's evaluation of BPSD more objective, partially eliminating recall bias through the use of a daily diary focusing on the most disturbing BPSD and their triggers. This would also overcome the limitation of the observation by the physician, which is limited to the short period of the visits and may not capture relevant phenomena present at home. A diary has already been used in another recent study, with a checklist based on NPI in one case (Cho et al., 2021), and a rather long checklist of 53 behaviors in another one (Fauth et al., 2006). However, none of these approaches was treatment-oriented, and triggers were not evaluated. Therefore, we expect that our instrument, called “BPSDiary,” would allow a more precise and treatment-oriented assessment of BPSD, providing physicians with relevant data to implement non-pharmacological and tailored strategies to address them and eventually reduce caregivers' burden.

## 2 Methods and analysis

Based on the premises mentioned above, we present here the protocol for a non-pharmacological parallel-arm randomized controlled trial named “Use of a Diary to Assess and Monitor Behavioral and Psychological Symptoms of Dementia.” The study will randomize 300 dyads (persons with dementia and their caregivers) to either the use of the BPSDiary to record BPSD or usual care. In this context, usual care means the way involved physicians usually treat their patients, according to existing guidelines, personal experience, or both. The main objective is to evaluate whether the use of the BPSDiary can lead to a significant reduction of ZBI scores at 3 months compared to usual care.

Inclusion criteria will be as follows:

- Adult patients with cognitive impairment (either MCI or dementia, either neurodegenerative or vascular or both, diagnosed by a physician with experience in dementia care)- Willingness of both caregiver and patient to take part in the study- Caregiver living with the patient, or able to cover the whole day (e.g., caregiver living in the same building)- Presence of BPSD pertaining to the HIDA domain, as inferred by the physician during the screening visit- Signed informed consent from both patient and caregiver, as requested by the ethical committee

Dyads will be excluded if they do not provide written consent to participate in the study.

The study will be conducted across the Centers for Dementia and Cognitive Decline of nine Italian centers, distributed along the peninsula. These centers have been selected based on their regional importance and expertise in managing BPSD. Sixty patients will be recruited at the Fondazione IRCCS San Gerardo dei Tintori (Monza, Lombardy), while 30 patients each will be enrolled in the remaining centers. These will include the following eight centers: Fondazione IRCCS Don Gnocchi (Milan, Italy), IRCCS Fondazione Mondino (Pavia, Italy), Ospedale Multimedica (Castellanza, Lombardy), AO Padova (Padova, Veneto), AOU Careggi (Florence, Tuscany), Sapienza University (Rome, Lazio), Ospedale SS Annunziata (Chieti, Abruzzo), Pia Fondazione Cardinale Panico (Bari, Apulia). The geographical distribution of the involved centers is shown in Figure 1.

**Figure 1 F1:**
[figure not shown]
Geographical distribution of involved centers. From North to South: Castellanza (west), Monza (east), Milan, Pavia, Padua (east), Florence, Chieti, Rome, Bari.

The dyads will be randomized in a 1:1 allocation ratio with a process of covariate adaptive randomization (Suresh, 2011), using caregiver age (cut-off 60 years old; this cut-off is chosen to ensure an equal representation of young/middle-age and elderly caregivers), patient comorbidity [Cumulative Illness Rating Scale (CIRS) – comorbidity index (Salvi et al., 2008) cut-off of 1], patient gender, patient functional independence [Activities of Daily Living (ADL) and Instrumental Activities of Daily Living (IADL) preserved vs. either of them not preserved] and baseline ZBI (cut-off of 31 points). Randomization will be performed through a dedicated software, as previously shown by other groups (O'Callaghan, 2014; Guillaumes and O'Callaghan, 2019).

At baseline, the following scales will be administered to the dyads: CIRS, ADL, IADL, NPI, ZBI, MMSE. These scales will be administered in a quiet environment, free of distractions. Data will also be gathered on age, gender, education of both caregivers and patients, and drugs used by the patients.

The caregivers randomized to the intervention arm will be instructed to use the BPSDiary to register specific behaviors of interest (the BPSDiary is available in the Supplementary material). These include insomnia, agitation/anxiety, aggression (either physical or verbal), purposeless motor behavior, delusions/hallucinations. The caregiver will have to mark any occurrence of these BPSD by indicating the time of onset, ticking the appropriate severity box (mild or severe) and writing down possible triggers. An introductory page explains the definitions of each term in plain language and provides examples. The data in the diary are then transposed on an interactive excel file (available at https://drive.google.com/file/d/1i3_NY7MRg9uoe2kD5njkUhax1zS9engp/view?usp=sharing) that allows the treating physician to analyze several aspects of the BPSD of the patient, such as their temporal pattern, severity, prevalence and triggers. The BPSDiary is only offered in a “paper and pencil” version, to avoid issues related with poor digital skills of elderly caregivers in Italy.

After the first 6 weeks the caregiver will be contacted by telephone and he/she will be asked if there are any issues related to BPSD. Caregivers randomized to the intervention arm will be asked to send the first six pages of the diary for analysis. Appropriate actions will be taken to address any issue according to the treating physician's judgment; options may include telephone counseling, scheduling a visit, prescribing or deprescribing drugs and so on. All of this will be repeated after other 6 weeks. All the approaches will be recorded and accounted for in the analyses.

The following scales will be re-administered at the end of the study (3 months): NPI, ZBI, and the satisfaction questionnaires (available in the Supplementary material). The other scales (ADL, IADL, MMSE) will not be administered, as they are judged unlikely to significantly change in the study period, and even if they do, this would probably not be related to the use of the diary.

The caregiver will be allowed to contact the treating physician at any time during the entirety of the study in case urgent actions need to be taken to address BPSD; dyads randomized to the diary will be asked to send it to the doctor for analysis. Actions taken during these unscheduled contacts will be registered in the following scheduled contact window (e.g., if the contact takes place at week 4 and quetiapine is introduced, this will be registered at the first of the two scheduled contacts at week 6).

The primary outcome will be the variation on the ZBI at 3 months. Secondary outcomes will include variation on NPI, olanzapine equivalents [calculated with the Defined Daily Doses method (Leucht et al., 2016)], caregiver care-related satisfaction, and variation on relevant NPI-distress scores at 3 months, as well as caregiver and physician diary-related satisfaction. Relevant NPI-distress scores include scores related to insomnia, agitation, aberrant motor behavior, aggression, delusions, hallucinations (i.e., the domains assessed in the BPSDiary).

The entire study will last 13 months. Enrollment will take place over the course of 9 months, and each dyad will be followed for 12 weeks. Data analysis is expected to take another month.

Sample size has been computed with the software gpower (Erdfelder et al., 2009) considering a clinically significant difference of at least 6 points at the ZBI, corresponding to an effect size of 0.428 with a *t*-test. Considering α = 0.05 and β = 0.05, 238 would be required. We hypothesized a drop-out rate of 20%, based on clinical experience on similar studies; therefore, 300 dyads are required. The power graph is shown in Figure 2.

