**Figure 2 F2:**
[figure not shown]
Power graph for sample size calculation.

A *t*-test will be used to compare differences in ZBI variations (ZBI_followup_-ZBI_baseline_) between the two arms. A *t*-test will be also used to compare differences between the two arms in NPI, NPI-distress, olanzapine equivalents variations, as well as satisfaction questionnaires scores. Pre-specified analyses will include linear mixed effect models to compare ZBI trajectories, including arm, person's and caregiver's age, baseline MMSE, person's and caregiver's education, and olanzapine equivalents as possible predictors.

The registration data set is reported in Table 1. The CONSORT checklist (Schulz et al., 2010) for this RCT is available in the Supplementary material.

**Table 1 T1:** Registration data set.

**Data category**	**Information**
Primary registry and identifying number	ClinicalTrials.gov, NCT05977855
Date of registration	August 7^th^, 2023
Primary sponsor	University of Milano-Bicocca
Sources of monetary or material support	University of Milano-Bicocca
Contact for public or scientific queries	[name] [name] [[contact]], Fondazione IRCCS San Gerardo dei Tintori, Monza, Italy
Scientific title	Use of a diary to assess and manage Behavioral and Psychological Symptoms of Dementia [BPSDiary]
Countries of recruitment	Italy
Health condition or problem studied	Behavioral and psychological symptoms of dementia
Intervention	Diary to record five different BPSD vs. Standard of Care
Key inclusion and exclusion criteria	Inclusion criteria: - Neurodegenerative or vascular cognitive impairment (MCI or dementia) - Willingness of both caregiver and patient to take part in the study - Caregiver living with the patient, or able to cover the whole day - BPSD pertaining to the HIDA domain - Signed informed consent • Exclusion criteria: - Refusal to take part in the study
Study type	Interventional, non-pharmacological • Allocation: randomized • Masking: none • Primary purpose: treatment
Planned begin of enrollment	September 2023
Target sample size	300
Recruitment status	Recruiting
Primary outcome	ZBI variation at 3 months
Key secondary outcomes	- NPI variation - Olanzapine equivalents variation - Caregiver care-related satisfaction - NPI-distress variations^*^ - Caregiver and physician diary-related satisfaction

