## 3 Discussion

Several guidelines suggest the use of non-pharmacological interventions as a first line in the treatment of BPSD. However, the use of antipsychotics and other psychoactive medications is still common in Italy (Azermai et al., 2013), and this might be dependent on the fact that addressing triggers of disruptive behaviors is hard and heavily influenced by recall bias. Moreover, it seems that caregivers perceive systemic barriers in non-pharmacological interventions which are partially dependent on the inability of physicians to provide information, support, and coaching about such strategies (Kerns et al., 2018). On the contrary, caregivers might have the wrong idea that psychotropic medications are generally safe and effective, as they may not be aware of FDA black-box warnings on antipsychotics (Kerns et al., 2018). The use of the BPSDiary could theoretically allow for the identification of such triggers, which would help the clinician finding tailored non-pharmacological solutions for the management of BPSD. Moreover, it could allow caregivers to reflect on the mechanisms and causes of behaviors, which might give them a sense of empowerment.

A strength of our protocol is the representation of almost all Italian peninsula. Thanks to the variety of customs and societal characteristics in different Italian regions, the inclusion of centers representative of Northern, Central, and Southern Italy, as well as serving both Italian biggest cities (such as Rome and Milan) and smaller realities (such as Castellanza) will allow exploring the use of the diary in diverse settings, drawing considerations about its reception, adaptability, and implementation. This is important, as several disparities among Italian regions and contexts, such as living conditions, education, and social isolation, which are associated with varying levels of reported health (Franzini and Giannoni, 2010), may also influence the assessment and management of BPSD. Another strength is the large anticipated sample size, that will incidentally allow exploring secondary outcomes, as well as analyzing the effect of different variables such as specific dementia type to evaluate which kind of patient might benefit the most from the intervention.

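### Centre is absent from the listed randomisation factors, the primary t-test and the listed mixed-model predictors; the t-test stays valid, but a centre term is a cheap improvement

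*Protocol article*

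**What the plan says.** All of the design text is in section 2 (Methods and analysis) of the protocol article.

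- **Centres.** There are "nine Italian centers, distributed along the peninsula". One enrols 60 dyads, "while 30 patients each will be enrolled in the remaining centers".
- **Comparator and management.** The article says "usual care means the way involved physicians usually treat their patients, according to existing guidelines, personal experience, or both". Actions after each telephone contact are left to the treating physician in both arms.
- **Allocation.** "The dyads will be randomized in a 1:1 allocation ratio with a process of covariate adaptive randomization". The list starts with caregiver age, goes on to the comorbidity index, patient gender and ADL/IADL independence, and ends "and baseline ZBI (cut-off of 31 points". Centre is not in it. The article says that dedicated software is used, but not whether it runs centrally or separately at each site.
- **Analysis.** The primary analysis is a t-test on the change in ZBI. The same test is used for NPI, NPI-distress, olanzapine equivalents and satisfaction. In addition, "Pre-specified analyses will include linear mixed effect models to compare ZBI trajectories"; the possible predictors named are arm, both ages, baseline MMSE, both education levels and olanzapine equivalents. No random effects are described.
- **Reason to expect centre differences.** The Discussion (section 3) says that disparities among regions and contexts "may also influence the assessment and management of BPSD", and presents the geographic spread as a strength.

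**The concern.** The article gives its own reasons for expecting centre to matter: a comparator defined by what each physician does, discretionary management in both arms, no masking, and regional differences that may affect assessment and management. Neither the stated allocation scheme nor the stated primary test uses centre.

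Two things follow if allocation ignores centre. First, the arms can by chance be unequal within a centre, so part of an observed difference may reflect where dyads were seen. Second, between-centre variation in ZBI change stays in the error term. Olanzapine equivalents are the most exposed secondary outcome, because local prescribing habit enters them directly.

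At stake are the precision of the primary contrast and how readily a reader can separate the diary from local practice.

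**Working it through.** **Inputs from section 2.** Centre sizes 1 × 60 + 8 × 30 = 300; target difference 6 ZBI points, effect size 0.428, so implied SD = 6/0.428 = 14.02; alpha 0.05; beta 0.05; 238 evaluable; 20% drop-out, so 300 × 0.80 = 240 completers.

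**Assumption.** The ICC is the share of variance in ZBI change that lies between centres. The documents do not give it; 0 to 0.20 is used.

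**1. The plan's own figure.** Per arm, n = 2(1.645 + 1.645)²/0.428² = 118.2, rounded up to 119, so 238 in total. This reproduces the stated figure, but only with a one-sided alpha of 0.05. Two-sided, the same formula gives 142 per arm (284), and 120 per arm has 91% power. The sidedness is a separate matter; two-sided 0.05 is used for power below.

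**2. Imbalance if allocation ignores centre** (treated as independent 1:1 within each centre).

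- One centre of 30 splits 20:10 or worse: 2 × P(X ≤ 10), X ~ Binomial(30, 0.5) = 0.0987.
- At least one of eight such centres: 1 − (1 − 0.0987)⁸ = 0.56.
- For 21:9 or worse the figures are 0.043 and 0.30.

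**3. What such an imbalance does to the estimate.** A one-SD centre effect is 14.02 × √0.05 = 3.1 points at ICC 0.05, and 14.02 × √0.10 = 4.4 points at ICC 0.10. A 20:10 split in one centre shifts the arm difference by (20 − 10)/150 of that, which is 0.2 to 0.3 points. Over all nine centres the SD of the shift is √300/150 = 0.115 times the centre SD, or about 0.4 to 0.5 points, against a 6-point target.

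**4. Type I error of the plain t-test** (simulation, nine centres, 238 analysed, one-sided 0.05).

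- Allocation ignoring centre: 0.049 to 0.053 for ICC 0 to 0.20.
- Allocation balanced by centre, analysis unadjusted: 0.047 at ICC 0.05, 0.040 at 0.10, 0.038 at 0.20. A fixed centre effect brings these back to 0.047 to 0.052.

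**5. Power** (simulation, 240 completers, two-sided 0.05, effect size 0.428, allocation ignoring centre).

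| Assumed ICC | Plain t-test | Fixed centre effect | Change (points) |
|---|---|---|---|
| 0 | 91.3% | 90.3% | −1.0 |
| 0.05 | 91.3% | 91.6% | +0.3 |
| 0.10 | 91.6% | 93.0% | about +1.5 |
| 0.20 | – | – | about +3.5 |

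Dividing the effect size by √(1 − ICC) gives 0.428/√0.95 = 0.439 and 0.428/√0.90 = 0.451, and so power of about 92% and 94%. That shortcut is too favourable: it leaves out the information lost when a centre effect is estimated with allocation that is not balanced by centre.

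**The case against.** The strongest case against acting is that nothing is broken. Randomisation protects the t-test on average, its standard error already contains the chance imbalance, and the gain in power is small or negative unless the ICC reaches about 0.10. The outcome is a change score, which already removes stable centre differences in ZBI level, so a large ICC cannot be presumed. All of this stands, and it limits the size of the point.

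Four stronger readings are tempting, and the documents do not support them.

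- *That the primary comparison is biased or invalid.* Step 4 shows nominal error when allocation ignores centre.
- *That centre is missing from every analysis.* The mixed model's random effects are not described, and the analysis plan, which is not shown, may include centre there. What this article fixes is the allocation list, the t-test and the listed predictors.
- *That the centres are known to practise differently.* The Discussion says only that regional disparities may have an influence, and section 2 says the centres were chosen for expertise in managing BPSD.
- *That the 56% shows serious confounding.* It assumes that allocation is not run separately by centre, which the article does not settle, and step 3 shows how little one such split moves the estimate.

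One part of the objection does not stand: leaving the matter to the analysis plan. A two-sample t-test cannot carry a centre term, so an analysis plan that adjusts for centre would have to change the primary analysis stated here.

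**Conclusion.** The point holds as a modest matter of efficiency and credibility, not of validity. The listed allocation factors, the primary t-test and the listed mixed-model predictors leave out centre, although the article itself gives grounds to think that centre may matter.

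If allocation ignores centre, the price is chance within-centre imbalance and lost precision, worth between about −1 and +3.5 points of power over an assumed ICC of 0 to 0.20. If allocation is run by centre, the t-test is conservative (about 0.04 at ICC 0.10), and a centre term restores about 0.05. A centre term is therefore reasonable under either reading of the allocation procedure.

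One limit remains. If the diary's effect itself differs between centres (assumed SD 0.1 to 0.2 of the outcome SD, ICC 0.05), one-sided type I error for the average effect rises to about 0.057 to 0.075. A fixed centre main effect does not cure that (0.058 to 0.076).

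**What to change.** Before the data are analysed, replace the primary t-test on ZBI change with a linear model containing arm and centre, with centre as a random intercept or as a fixed effect with eight degrees of freedom. Use the same form for the secondary outcomes and name centre in the mixed model. State whether the randomisation software runs centrally or by site.

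The cost is a change of wording, with no new data and no change to the 300. With a fixed effect, up to about one point of power is lost if centres do not differ. A random intercept should largely avoid that loss, though this was not simulated.

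Adding centre to the randomisation algorithm is optional. Table 1 gives the trial as recruiting and unmasked, so this would be a mid-recruitment change, and it may make the next allocation easier to guess at sites of 30 dyads. The analysis change does not depend on it.

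### The 238-dyad requirement matches only a one-sided 5% t-test, which the visible text never declares; a two-sided 5% test has about 91% power, not 95%, after the planned 20% drop-out

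*Protocol article*

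**What the plan says.** All places are in section 2 (Methods and analysis) of the protocol article.

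- **Objective:** whether the diary "can lead to a significant reduction of ZBI scores at 3 months compared to usual care".
- **Allocation:** "The dyads will be randomized in a 1:1 allocation ratio".
- **Target difference:** the calculation was done in G*Power, "considering a clinically significant difference of at least 6 points at the ZBI", "corresponding to an effect size of 0.428" for a t-test.
- **Error rates and result:** "Considering α = 0.05 and β = 0.05, 238 would be required".
- **Inflation:** "We hypothesized a drop-out rate of 20%, based on clinical experience on similar studies; therefore, 300 dyads are required".
- **Primary analysis:** a t-test "will be used to compare differences in ZBI variations" between the two arms, the variation being follow-up minus baseline.

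Neither the sample size paragraph nor the analysis paragraph says whether the test is one-sided or two-sided.

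**The concern.** Once effect size, α, β and a 1:1 allocation are fixed, the size of a two-sample t-test depends on only one further choice: one side or two. The article does not state that choice, yet its figure of 238 depends on it.

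There are two possibilities.

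- **The analysis will be two-sided at 5%.** The trial then does not have the β of 0.05 by which its size is justified.
- **The analysis will be one-sided at 5%.** The chance of wrongly declaring the diary beneficial is then 5%, against 2.5% in that direction under a two-sided 5% test, and the visible text does not tell the reader so.

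Leaving the matter open has a practical consequence. A favourable result with a two-sided p-value between 0.05 and 0.10 could be called significant by pointing to the sample size calculation, or non-significant by pointing to convention. The registration data set (Table 1) gives masking as none, and burden is reported by the caregiver, so the error rate of the primary test should be fixed before the data are compared.

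**Working it through.** **Inputs, all from section 2 of the protocol article:** d = 0.428; α = 0.05; power = 1 − β = 0.95; 1:1 allocation; drop-out 20%; 300 randomised. Sidedness is not given, so both cases are computed.

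**Method.** For n completers per arm, the t statistic has df = 2n − 2 and noncentrality λ = d·√(n/2). One-sided power is P(T > t at 1 − α). Two-sided power is P(|T| > t at 1 − α/2). T follows the noncentral t distribution with parameters df and λ.

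**Step 1. Reproduce the stated 238 (one-sided, α = 0.05).**
- n = 118: power 0.9488, just short.
- n = 119: df = 236, λ = 0.428 × √59.5 = 3.301, critical t = 1.651, power 0.9502.
- The total is 2 × 119 = **238**, an exact match.
- Drop-out: 238 / 0.80 = 297.5, so 298, rounded up to 300. This also agrees with the article.

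**Step 2. The same inputs, two-sided at α = 0.05.**
- n = 142: power 0.9489, just short.
- n = 143: df = 284, λ = 0.428 × √71.5 = 3.619, critical t = 1.968, power 0.9502.
- The total is 2 × 143 = **286**. That is 286 − 238 = 48 more completers, or 20% above the stated figure.
- Drop-out: 286 / 0.80 = 357.5, so 358 randomised.

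**Step 3. Rule out rounding of the effect size.** With d = 6/14 = 0.4286 in place of 0.428, the results are again 238 one-sided and 286 two-sided.

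**Step 4. Two-sided 5% power at the planned size (d = 0.428).**

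| Completers | Basis | Two-sided power | β |
|---|---|---|---|
| 238 | stated requirement | 90.8% | 0.092 |
| 240 | 300 × 0.80 | 91.0% | 0.090 |
| 270 | 300 × 0.90 (10% drop-out, for illustration) | 93.9% | 0.061 |
| 300 | no drop-out | 95.9% | 0.041 |

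**Step 5. The same gap in ZBI points.** The article gives no standard deviation. The implied value is 6 / 0.428 = 14.02. With 240 completers, two-sided 95% power is reached at d = 0.467, which is 0.467 × 14.02 = about 6.55 points instead of 6.

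**The case against.** The case on the other side has several parts.

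**The sample size paragraph is internally consistent.** The figure of 238 follows exactly from the stated inputs under a one-sided test, and 300 follows from 238. This stands. A reader might infer from the mismatch with 286 that the calculation contains an arithmetic error; the documents do not support that.

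**The objective is directional.** It speaks of a reduction in ZBI scores, which is compatible with a one-sided test. That is so, but naming the hoped-for direction does not define a test. The analysis paragraph says only that differences will be compared, and uses the same t-test without any direction for the secondary outcomes.

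**Sidedness may be stated elsewhere.** The power graph in Figure 2 and the supplementary material were not available, and a condensed article may leave such detail to a fuller document. This limits the claim to the visible text, and a reader should not conclude that the sponsor concealed a one-sided test. It does not remove the point. A published figure that holds only under an unusual setting should carry that setting beside it. A fuller document that specified a two-sided 5% test would contradict the published β.

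**The power loss is small and depends on drop-out.** This also stands. The 91% applies after the full assumed 20% loss; with every dyad analysed, two-sided power exceeds 95%. A reader might conclude that the trial is underpowered or must recruit to 358. Power above 90% for the stated difference does not support that.

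**Conclusion.** The concern holds as a mismatch between the sample size calculation and the primary test as an ordinary reader would understand it. The 238 requires a one-sided 5% t-test, and no visible text declares one.

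If the primary t-test is two-sided at 5%, β at the planned size is about 0.09, nearly double the stated 0.05. This rests on the article's own effect size of 0.428, equal arms and 20% drop-out. If a one-sided 5% test is intended, 238 and 300 are correct, and the defect is that the choice is neither stated nor justified.

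The severity is moderate: it should be fixed, but it does not threaten the trial. The main reason to act is to fix the error rate of the primary comparison before the data are seen; the loss of about four percentage points of power is secondary.

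**What to change.** Before outcomes are compared between arms:

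1. State in the analysis paragraph that the primary t-test on ZBI change is two-sided at 5%.
2. Keep 300 dyads and restate the planning sentence to this effect: 300 randomised dyads, with 240 expected completers after 20% drop-out, give about 91% power to detect a 6-point difference in ZBI change (d = 0.428) with a two-sided t-test at α = 0.05. If a standard deviation is added, 14.0 should be marked as inferred from 6 / 0.428 unless the sponsor can confirm the value used.
3. If a one-sided 5% test was intended, declare and justify it for the primary analysis, leave 238 and 300 as they are, and report the primary result as one-sided at 5%. The declaration need not extend to the secondary outcomes, which the sample size calculation does not concern.

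The cost is a sentence or two in the protocol and the analysis plan. No extra dyads are needed. The only downside of the two-sided statement is a slightly less favourable stated power.
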